In the Phase I dose escalation trial, sevuparin was found to be safe and well-tolerated with minimal effects on APTT at doses of 1.5 mg/kg and 3mg/kg every six hours but a dose of 6.0 mg/kg led to higher APTT values. The Data Monitoring Committee (DMC) therefore recommended that the study should continue to the Phase II with a dose of 3.0 mg/kg sevuparin every 6h, given the potentially increased risk of adverse events at higher doses
^
42
^.

In the Phase II trial, sevuparin was administered as an intravenous infusion over 5 minutes in addition to standard care i.e., a fixed dose combination of 1000 mg atovaquone and 400 mg proguanil once daily for three days, in subjects with uncomplicated
*P. falciparum* malaria (experimental arm), as compared to atovaquone/proguanil treatment alone (control). There were minimal and non-clinically relevant changes in anti-Xa- and prothrombin-times, and the international normalized ratios associated to the sevuparin dose. Increases in APTT were dose-dependent and appeared to follow the time-concentration curve for each sevuparin infusion. The 6-hour interval between the infusions allowed for nearly full reversibility of APTT levels after each dose, and no accumulative effects were seen over the course of the 12 consecutive infusions. Thrombocytopenia occurred in one subject but was noted to be present before the initiation of sevuparin treatment. There was no incident of bleeding in any of the participants nor were there any other serious adverse events or adverse events
^
42
^.

Sevuparin was therefore judged to be safe and well tolerated in adults with mild malaria and was found to safe with minimal side effects in other clinical trials
^
43
^. It led to a reduction in numbers of ring-stage infected erythrocytes after a single sevuparin infusion and resulted in a transient appearance of mature parasite infected erythrocytes (schizonts appearing in the circulation, indicating these had been released after desequestration). These both occurred within one hour after the first sevuparin injection. Thus, these studies indicate that a novel new drug candidate for adjunctive treatment of severe malaria had been identified that blocks merozoite invasion and transiently de-sequesters infected erythrocytes in humans with uncomplicated
*P. falciparum* malaria.

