^, will be sought from parents/guardians by the admitting medical team. Following verbal assent, written informed consent will be sought from the parent as soon as possible once the child’s clinical condition has stabilized.

The participant information sheet, consent form and case report files can be found as
*Extended data*
^
62
^.

**
*Trial treatments.*
** We aim to study 20 children (See
Figure 1 Trial Flow). The trial will be open label with clinicians aware of study drug dosage. Laboratory staff performing APPT levels will be blind to drug dosage. All children will receive standard care including parenteral artesunate. Sevuparin will be given as three infusions at 0, 8 and 16 hours after enrolment. The initial participants (two ‘cohorts’ of 2 children each, i.e., 4 children in total) will receive a dose of 1.5 mg/kg/dose with the plan to escalate up to the next highest dose up to a maximum of 6.0 mg/kg/dose for subsequent children. In order to determine whether, and the rate of escalation, to move to a higher dosage for subsequent patients after the first 4 children we will use a design called the Continuous Reassessment Method (CRM). This starts with an
*a priori* dose-toxicity curve, reflecting the probability of experiencing a toxicity event (here APTT>2.5xULN 1h after any of the three doses) to the dose received. In this method of dose finding, the dose-toxicity curve is re-fitted to the data after each child is enrolled, based on their observed dose and whether they had a dose limiting toxicity event. After the first 4 children, each subsequent patient would be assigned the next highest dose, until the estimated risk of toxicity is just below or at the target toxicity level, designated as the maximum tolerated dose (MTD). The dose limiting toxicity (grade 3 APTT, >2.5xULN),
*a priori* dose-toxicity curve and chosen target toxicity rate (15%) used in this trial have been based upon data shared by the investigators from the adult sevuparin studies in Thailand [36]. In particular, almost all adults enrolled in this trial experienced grade 2 toxicity after one or more sevuparin doses, but APTT rapidly normalized, hence the choice of grade 3 toxicity to define the MTD in this dose-finding trial. APTT 24h post-enrolment is a key secondary safety endpoint to confirm rapid normalization.

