**Figure 1. f1:**
[figure not shown]
Trial Flow

Any child with APTT>2.5xULN 1h after a dose of sevuparin will immediately discontinue trial treatment (and it would be counted as a toxicity event). They will continue to be followed according to the trial schedule (on-study, off-study-drug), to confirm resolution of APTT and to record clinical outcomes.

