### Clinical assessments

Members of the clinical team and study team will all receive pre- and peri-trial training on the management of severe malaria. A manual of operations for the trial will be available for the study team, to anticipate and troubleshoot any potential issues. Vital signs will be monitored regularly (including temperature, heart rate, respiratory rate, blood pressure, oxygen saturation, conscious level). These will continue twice-daily after 24 hours until the child is discharged from HDU. All children will be managed on the HDU until conscious and able to take and retain oral fluids/food. During the period of sevuparin administration (0–24 hours) children in Kilifi, Kenya will have continuous electrocardiogram (ECG) monitoring for safety. However, it is notable that the trial in Thai adults showed no signs of QT prolongation
^
42
^. Once discharged from HDU children will be reviewed daily until discharge and followed up at day 7 and day 28. On admission and Day 28 children will be assessed by an adapted Kilifi Developmental Index to assess developmental status and clinically for neurodevelopmental sequelae (see
Table 2). Non-compliance is limited by the intervention being administered by clinical teams during admission. Any child who develops APTT>2.5xULN (grade 3 toxicity) will not receive further doses of sevuparin but will continue to be followed up. Children lost to follow-up before day 28 will be traced for vital status (permission requested within consent) using locator data and multiple contact phone numbers recorded before discharge.

**Table 2. T2:** Clinical management schedule.

	Assessment Time										
Procedure	Adm	1h	2h	4h	8h	9h	17h	24h	Bi daily to discharge	Day 7	Day 28
Clinical assessment	X	X	X	X	X			X	X	X	X
ECG continuous to 24 hours (Kilifi)	X							X			
APTT and coagulation tests (ACT) (1.7ml)	X	X 1 hr post dose				X 1 hr post dose	X 1 hr post dose	X			
Microperfusion ^ & ^	x					x	x				
Lactate (point of care)	X	X				X		X			
Standard clinical test non-research (FBC, POC chemisty Istat) *	X								X		X
Malaria slides	X					X		X	(36,48, 72 hrs)	X	X
Stored red cells & admission plasma **	X					X					X
PK sample		X				X					
Neuro-developmental assessment	X										X

^&^ Kilifi Site only

* Standard- non research clinical tests full blood count, clinical chemistry POC iSTAT (electrolytes, pH BUN) will be done at admission and at 24 hours and Day 7 (Full blood count only).

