### Safety endpoints

APTT 24h post enrolment (absolute level and grade)

Development of abnormalities of coagulation indices (prothrombin) (Grade 2 and above)

Neurological sequelae through day 28

Mortality through day 28

Serious adverse events through day 28

Grade 3/4 adverse events through day 28

APTT 24h post enrolment will be used as an assessment of normalization 8h after the final sevuparin dose. Both absolute levels and grade will be considered.

De-novo evidence of neurological sequelae will be ascertained using a modified Kilifi Developmental Index
^
63
^ assessed at admission (to identify pre-existing conditions) and follow up (which we have adapted to use for the other trials.

Serious adverse events will use the standardized definitions (see section 11 below). SAEs will be independently reviewed in real-time by the DMC. Adverse events will be graded following the Common Toxicity Criteria v5.0: (
https://ctep.cancer.gov/protocoldevelopment/electronic_applications/docs/CTCAE_v5_Quick_Refe rence_5x7.pdf).

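### The 24 h APTT is read as 8 h after the final dose, which is untrue for children stopped after dose 1 or 2 and could flatter their recovery if reversal is slow

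*Protocol article*

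**What the plan says.** Three statements in the Protocol article have to be read together.

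- **Dosing** (Trial treatments, under Sample size determination): "Sevuparin will be given as three infusions at 0, 8 and 16 hours after enrolment".
- **Stopping rule** (text below Figure 1, repeated under Clinical assessments): "Any child with APTT>2.5xULN 1h after a dose of sevuparin will immediately discontinue trial treatment". These children stay under observation: "They will continue to be followed according to the trial schedule (on-study, off-study-drug), to confirm resolution of APTT and to record clinical outcomes".
- **Endpoint** (Safety endpoints): "APTT 24h post enrolment will be used as an assessment of normalization 8h after the final sevuparin dose". Absolute level and grade are both to be considered. Trial treatments gives the purpose: "APTT 24h post-enrolment is a key secondary safety endpoint to confirm rapid normalization".

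Table 2 schedules APTT at admission and at 1, 9, 17 and 24 h, and labels the 1, 9 and 17 h samples as one hour post dose. Protocol treatment discontinuation lists further reasons for stopping early and keeps such children in follow-up where possible.

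**The concern.** The endpoint is fixed by time since enrolment but interpreted by time since the last dose. The two agree only if dosing is complete, and the trial's own rule interrupts dosing in children whose APTT has risen most. A child stopped after dose 1 or 2 therefore has longer to recover before the 24 h sample, and that sample carries the same 8 h label as everyone else's.

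The error runs in one direction, since more time off drug can only make APTT look more normal. At stake is what the trial can say about how fast a grade 3 APTT resolves in severely ill children. The Statistical analysis section describes endpoints by means, medians or proportions and plans no subgroup analyses, so nothing stated there separates values taken 8, 16 and 24 h after the last dose.

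**Working it through.** **1. Interval from last dose to the 24 h sample.** Interval = 24 h minus time of last dose. The plan's own figure is reproduced first.

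- All three doses: 24 − 16 = 8 h, as stated.
- Stopped after dose 2: 24 − 8 = 16 h.
- Stopped after dose 1: 24 − 0 = 24 h.

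**2. Other samples already scheduled** (Table 2).

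- Stopped after dose 1: the 9 h sample is 9 − 0 = 9 h after the last dose.
- Stopped after dose 2: the 17 h sample is 17 − 8 = 9 h after the last dose.

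A near-equivalent of the 8 h value therefore exists for both groups, but no listed endpoint uses it for normalisation.

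**3. How many children.** Inputs from the article: 20 children and a target toxicity rate of 15% per child over three doses. Assumption: equal, independent risk at each dose.

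- Per-dose risk: q = 1 − 0.85^(1/3) = 0.0527.
- Probability of a DLT after dose 1 or 2: q + (1 − q)q = 0.1027.
- Share of DLTs that stop before dose 3: 0.1027 / 0.15 = 68%.
- Expected DLTs: 20 × 0.15 = 3.0. Expected early stops: 20 × 0.1027 = 2.05.
- Probability of at least one early stop: 1 − (1 − 0.1027)^20 = 0.885.

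On the same assumption, per-child DLT risks of 5% and 25% give 0.67 and 3.49 expected early stops. Without it, the early share can be anything from 0 to 100%, depending on which dose triggers the DLT. The count also treats all 20 children as being at target risk. If the first four, at the starting dose, contribute no DLTs, the expected figures are 16 × 0.15 = 2.4 DLTs and 16 × 0.1027 = 1.64 early stops.

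**4. Does the timing change the APTT?** The article gives no half-life, so this is illustration only. Assumptions: baseline 1.0×ULN, 2.5×ULN one hour after the last dose, and exponential decline of the excess with half-life h. Then APTT(t) = 1 + 1.5 × 2^(−(t−1)/h), in ×ULN.

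| Half-life (assumed) | Excess left at 6 h | 8 h | 16 h | 24 h |
|---|---|---|---|---|
| 1.5 h | 10% | 1.06 | 1.00 | 1.00 |
| 3 h | 32% | 1.30 | 1.05 | 1.01 |
| 6 h | 56% | 1.67 | 1.27 | 1.11 |
| 8 h | 65% | 1.82 | 1.41 | 1.20 |

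The first row is closest to the adult finding in the SEVUPARIN section: "The 6-hour interval between the infusions allowed for nearly full reversibility of APTT levels after each dose". There the timing makes almost no difference. At 6 h or longer, a child still well above normal at 8 h looks much closer to it at 16 or 24 h.

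**The case against.** The strongest reply has four parts.

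- **Reversal may be fast.** The only evidence in the article is the adult statement quoted above, and on that evidence samples at 8, 16 and 24 h give much the same answer. This stands as a limit on size: actual overstatement is not shown. It does not remove the point, because those adults had uncomplicated malaria, and the endpoint exists to check whether rapid reversal carries over to severely ill children.
- **The grade 3 threshold is not undermined.** A reader might infer that the mistiming weakens the reason for setting the DLT at grade 3. The article does not support that. The stated reason is that adults with grade 2 toxicity normalised quickly. Grade 2 does not trigger the APTT stop, so such children normally complete dosing and their 24 h value is correctly timed at 8 h.
- **Resolution is followed anyway.** A reader might also infer that early recovery after a DLT goes unmeasured. It does not: these children stay on the schedule to document resolution, and the DMC reviews data after each DLT. This stands as to data collection. The fault is confined to the definition and interpretation of the endpoint.
- **Analysis by doses received belongs in an SAP.** That is fair for the layout of summaries. It does not cover an unqualified statement in the protocol that is untrue for children stopped under its own rule.

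**Conclusion.** The point holds as a definitional error with a known direction and an unknown, possibly negligible, size. The 8 h reading is right for children who receive all three doses, including those with a DLT after dose 3. It is wrong for those stopped after dose 1 (24 h) or dose 2 (16 h), whether for a DLT or for another reason.

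About 2 of 3 expected DLT children in 20 would be affected. That rests on the 15% target applying to all 20 and on equal independent per-dose risk. The consequence for APTT depends on a paediatric reversal rate that the article does not give. The supportable conclusion is that the endpoint could overstate how quickly a grade 3 APTT resolves if reversal is slower than in adults, not that it does. The primary endpoint, the dose-toxicity updating and the MTD are untouched.

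**What to change.** Redefine the normalisation endpoint as APTT, level and grade, about 8–9 h after the last sevuparin dose received:

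- one dose received: the 9 h sample;
- two doses received: the 17 h sample;
- three doses received: the 24 h sample.

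Apply this to every early stop, whatever the reason. Report children with and without a DLT separately, and keep the 24 h APTT for all children as a descriptive measure labelled by time since enrolment. Because Table 2 labels the 9 h and 17 h samples as post-dose, add a note that they are taken at those clock times in children who are off drug.

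The cost is a few sentences of wording. No sample, visit or change to treatment is added, since these children already remain on the trial schedule.

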### SAEs and interim analyses

SAEs will be reviewed immediately by a designated physician (SAE reviewer) and reported to the appropriate ethics and regulatory committees within one week. The Chief Investigator will inform the Trial Steering Committee (TSC) and Data Monitoring Committee (DMC) for review on a regular basis (as deemed necessary). The DMC will review data after the first 2 ‘cohorts’ of 2 children each have been enrolled to the lowest dose, and then after each Dose Limiting Toxicity event. [name] (Oxford) has agreed to be the Chairman is the DMC, other members will include an independent statistician and 2 pediatricians with relevant DMC or clinical trial experience. They will meet by regular teleconference. The continual reassessment method uses data from each enrolled participant to update the dose- toxicity curve and then suggests an escalation of dose to the largest dose with risk of estimated risk of toxicity below the target toxicity level if appropriate.

**
*Trial monitoring.*
** The trial will be monitored by the Clinical Trial Facility in Kilifi which oversees standards and the quality of all trials conducted through the KWTP and through its monitoring systems and standard operating procedures are organised to ensure that all sites can be monitored with equal independence and rigor. All monitors will be appropriately qualified and trained. At each monitoring visit the monitors will:

▪verify completeness of Trial Master File▪confirm adherence to protocol▪review eligibility verification and consent procedures▪look for missed clinical event reporting▪verify completeness, consistency and accuracy of data being entered on CRFs▪evaluate drug accountability▪provide additional training as needed

The monitors will require access to all patient medical records including, but not limited to, laboratory test results and prescriptions. The investigator (or delegated deputy) should work with the monitor to ensure that any problems detected are resolved.

### Data management

All clinical and laboratory data will be recorded in the CRFs and stored with a unique serial number identifier. Data will be entered onto Open Clinica. All electronic data will be regularly backed up and backup copies stored both on and off site. Paper records will be archived in locked cabinets. These cabinets will have limited access with prior authorisation. All data will be partially- anonymized prior to presentation or publication of any results. Archive documents will be sent for long term storage (10 years) at an appropriate facility according to national policies.

### Confidentiality

Participant’s identification data will be required for the registration process. All clinical and laboratory data will be recorded in the CRF and stored with a unique serial number identifier. Information will only be made available to those caring for the child and those directly involved with the study. Data will be entered onto Open Clinica (FDA approved, web-based application). All data will be regularly backed up and backup copies stored both on and off site. Paper records will be archived in locked cabinets. These cabinets will have limited access with prior authorisation. All data will be partially- anonymized prior to presentation or publication of any results. All clinical data will be held confidentially, and personal identifiers will be removed before analysis of the data and presentation of the results.

### Data sharing

After completion of the study, requests for data access from researchers outside the study team will be considered by a subgroup of the Centre Scientific Committee (Data Governance Committee), and where indicated, requestors will be asked to develop scientific protocols for approval of secondary analyses. The potential to share data will be included in the participant Information and Consent Form.

### Statistical analysis

Clinical data will be summarized using means and medians where appropriate for continuous data depending on the distribution. Primary and secondary endpoints will be described using means or medians or proportions. Analyses will follow intention-to-treat. As this is a Phase I trial no subgroup analyses are planned.

### Ethics statement

Ethical approval has been obtained from Kenya Scientific and Ethics Review Unit (SERU), Nairobi Kenya on 25th February 2019 (protocol number GCMR-C/127/3744), Imperial College Research Ethics Committee (ICREC) on 13
^th^ July 2021 (protocol number 18IC4513) and National Health Research Ethics Board, Lusaka, Zambia on 24
^th^ July 2023 (protocol number NHREB001/24/07/2023). The trial was registered on the Pan Africa Clinical Trials PACTR number: 202007890194806 on 20/07/2020) and ISRCTN reference no 32271864 on 28/07/2021. These were updated on 18
^th^ August 2023.

### Safety

The study will be performed in patients who may potentially benefit from the treatment. The risks of cannula insertion and blood drawing include pain, infection at the site of the cannula and thrombophlebitis. These will be minimised by careful technique according to a standard SOP, cannula site inspection and replacement or removal where necessary. No more than 1ml/kg of blood will be drawn for research at any one time. The trial will be recruiting patients with severe illness and likely a high mortality rate. At the start of the trial, the site will receive appropriate training on the use of Sevuparin and will have 2 dedicated clinicians. Sevuparin can lead to minimal and non- clinically relevant changes in APPT (grade II toxicity) In the Phase I dose escalation trial, sevuparin was found to be safe and well-tolerated with minimal effects on APTT at doses of 1.5 mg/kg and 3mg/kg every six hours but a dose of 6.0 mg/kg led to higher APTT values
^
42
^. The Data Monitoring Committee (DMC) therefore recommended that the study should continue to the Phase II with a dose of 3.0 mg/kg of sevuparin every 6h, given the potentially increased risk of adverse events at higher doses.

Risk will be minimised by the trial design/methods as described above under trial treatments. The escalation through the doses to find the maximum tolerated dose using the dose toxicity curve and data from children previously enrolled is carefully monitored by the DMC and Investigators.

### Benefits

All patients will be closely monitored so that clinical deteriorations can be identified at the earliest opportunity and appropriate therapy initiated. Prior to the start, the dedicated study teams will undergo detailed training on general management of severe malaria and its complications and receive very detailed training on the use of sevuparin. We believe this will afford all children enrolled in the trial with a higher quality of care. All routine non-trial medications required by the hospital to treat the child will be made available. Hospital bills for participants will be covered by the study (covering the costs for standard treatment for severe malaria and related complications). The parents or guardians for the children will be asked to return for a follow up clinic visit at day 7 and day 28 and thus will be offered continuing care for intercurrent illness, including any investigations or blood tests that are clinically indicated.

## Plans for dissemination of the study outcomes

### Public engagement

Community engagement will be through regular meetings with the community involving community representatives and county Health teams. At these meetings, information and feedback will be given and received. Information arising from the study will be fed back through hospital-wide meetings. This is a Phase I trial of an emergency intervention where our engagement has been at a scientific rather than public/community level. If a larger platform trial arose from this study, we aim to develop a dedicated and informed engagement strategy as part of this future trial. In general, we plan to feed into existing community engagement mechanisms. We aim to build general community awareness of research processes at the local hospital, and support community representative inputs into decisions around research design, consent procedures, patient information and trial conduct.

